## Abstract

**Background:**

In conflict-affected settings, access to health care for displaced populations is constrained by barriers including geographical, cultural, communication, logistical, financial and insecurity. A six year humanitarian crises in the North West and South West regions of Cameroon has caused 27% of health facilities to be non-functional. The eleven year crisis in North-East Nigeria, has caused the closure of 26% of health facilities. These closure of health facilities and population displacement led to health care delivery using humanitarian funding by multiple different agencies. However, there is a paucity of evidence on the selection and design of the primary health care delivery models used in humanitarian settings. To ensure efficient use of resources and quality of services, model of care selection should be evidence based and informed by the specific humanitarian context. This research protocol aims to explore how primary health care models are selected by humanitarian organizations.

**Methods:**

We will conduct a cross sectional quantitative survey to map the range of primary health care delivery models used by humanitarian organisations in Cameroon and Nigeria. Using in-depth interviews and focus group discussions with staff from humanitarian organizations and internally displaced persons, we will explore the factors influencing the selection of primary health care models in these settings and determine the coverage and gaps in services across the different primary health care models. Quantitative data will be analysed in a descriptive manner and qualitative data will be analysed thematically.

**Discussion:**

Different models of care have been reported to be used by humanitarian organisations in conflict-affected settings, yet evidence on how different models are selected is lacking. A detailed understanding of the rationale for selection, the design and quality considerations of the strategies used to deliver health care will be obtained using a survey, in-depth interviews and focus group discussions.

## Background

More than one billion people currently live in countries with protracted crises caused by violence, conflicts or disasters. More so, populations living in conflict-affected regions face barriers to health care including geographic, cultural, communication, logistical, financial and security barriers [1–4]. Current estimates show that 53% of deaths in children under 5 years, 45% of neonatal deaths, and 60% of preventable maternal deaths occur in fragile, violent or conflict settings (commonly termed humanitarian settings) [5]. Significant morbidity and mortality in these populations could be mitigated with strong primary health care-oriented systems [3]. In most cases, humanitarian organisations and government institutions provide primary health care to the conflict-affected communities using various models of care [3]. However, evidence around choice and quality of these delivery models in humanitarian settings remain insufficient [6, 7].

Researchers have identified the need to conduct rigorous research on primary health care (PHC) models of care to improve access to essential health care [8–10]. But limited guidance on how to select models of care weakens programming efforts and undermines quality [8, 11]. Further, communities have an important role to play in designing and implementing humanitarian responses for sustainability [8, 11–13], yet they are seldom consulted during program design. So, it is unclear what truly determines what model of care to use under what circumstances in conflict settings.

Moreso, humanitarian organizations are often pressured by the humanitarian imperative to rapidly provide life-saving interventions and by donors to make use of limited resources in responses, yet evaluation of the quality of care is rarely undertaken. For example mobile clinics are reported to be expensive and logistically difficult to implement [8, 14], yet they are commonly used to provide primary health care in conflict-settings. Also, the Global Health Cluster Quality of Care in Humanitarian Settings guidelines and WHO’s quality of care in fragile, conflict-affected publication include 07 domains of quality (people-centered, safe, equitable, effective, timely, integrated and efficient) [5, 15, 16]. However, these do not include metrics on how to select PHC models or provide a guide for evaluation for quality of services. Furthermore, there is little underpinning primary research and published evidence to inform these guidelines. Therefore, there is a need to add scientific evidence to guideline development.

In the North West and South West (NWSW) regions of Cameroon, since 2017, an armed crises has caused the displacement of over 679,000 persons and destruction of 37% (253/933) health facilities [17]. In North East (NE) Nigeria, one of the most severely protracted crises in the world, has continued for over 11 years with 7.9 million people requiring humanitarian assistance and 1.8 million persons displaced [18]. The humanitarian crisis in North East Nigeria has led to the closure of 26% of health facilities. This destruction of health facilities and mass displacement of populations in both countries, has severely curtailed access to health care for these populations. This has resulted in an influx of humanitarian health organizations in both countries, providing essential health care through various models of care at the primary health care level [18–20].

Evidence on what guides and determines the model of care selection under different circumstances in conflict settings is limited. Understanding current models of care and the premise behind the selection of the model, is the first step in improving primary healthcare access and quality of care delivery in conflict settings. To address the evidence gap, this research will explore how primary health care delivery models are selected by humanitarian organizations. To provide baseline information which informed this protocol, a systematic review and mapping desk review were conducted from December 2020 to June 2021. The systematic review was conducted to document the different primary health care models used in conflict-affected settings in Africa, which has been published in a separate manuscript (reference to follow). The systematic review looked at detail information on the models of care used including location of delivery, human resources used, implementing institutions, services offered, cost, accessibility, and challenges. The results showed that the models of care in place in these conflict-affected settings include health facility-based, community-based interventions, mobile clinics, outreach and home visits as shown in Table 1. Primary health care for internally displaced persons and refugees is provided by a wide range of actors including: international and national non-governmental organisations, governments, United Nations agencies, community-based organisations, faith-based organisations and academic institutions.

**Table 1 pone.0284957.t001:** Models of care definitions derived from systematic review study.

Model of care	Definition	Alternative names	Personnel used
Health facility based	*Services offered at a fixed facility*.	Health centres, Clinics	Health care workers, Community health works (CHWs)
Community-based interventions	*Services are offered in the community*.	Community-based interventions, Community health workers, village health teams,	CHWs
		community health volunteers, lady health workers and community based distributors;	
		Traditional birth attendants,	
Outreach	*Services are offered as an advanced fixed strategy ran by at least 02 health personnel attached to a health facility or organisation. The teams do not rotate or move from one community to another*	Community outreach, fixed outreach site, aid post	Health Care Workers, CHWs
Mobile clinic	*A*mbulatory *services are offered at the community-based on a rotating basis*.	Mobile teams, mobile health center, mobile health clinic, health camps,	Health care workers
Home-visit	*Services are offered in the homes of the patients/beneficiaries*	Households visits, house-to-house visits, tent-to-tent visits	Health Care Workers, CHWs

In this protocol paper, we provide preliminary data from the mapping review on the primary health care landscape in NWSW Cameroon and NE Nigeria which was conducted in January 2021. This mapping review involved a selection of technical documents including situational reports and bulletins. To obtain data on humanitarian organizations in NWSW Cameroon and NE Nigeria, the Relief Web database [21] and the MSF database [22] were used to search for Humanitarian Situation Reports (SiTREPS) and health cluster (sector) bulletins; both of these are key documents during humanitarian responses. Additional documents or data were obtained by asking key informants about potentially useful technical documents available for public use. Publications were selected by titles solely for full reading and data extraction. A total of 24 publications were explored and entered on an excel spreadsheet. Data collected for this preliminary mapping included the title of the publication, source of data, date of publication, name of organization, type of organizations, primary health care services offered, what model of care was used for the last two years (2018 to 2020) and the location of services (per district or Division). Further information about this mapping process is included in S1 and S2 Appendices.

Data obtained from the preliminary study enabled the development of the research protocol presented in this paper. The aim of this paper is to present the scope, and methods that will be used to understand what drives the choice of a specific primary health care model of care, and what are the quality gaps for chosen models of care in NWSW Cameroon and NE Nigeria. The specific objectives in this study are 1) to map the different primary health care models used by humanitarian organisations in conflict-affected settings of NWSW Cameroon and NE Nigeria; 2) to explore the factors influencing the selection of primary health care models in this settings; and 3) to determine the coverage and gaps in services.

## Methods

### Study aim

This research protocol aims to explore how primary health care models are selected by humanitarian organizations.

### Study design

In order to evaluate the complex and multifaceted issues present in primary health care delivery to conflict-affected communities, this research will use a sequential explanatory mixed methods designs which begins with a quantitative phase using a survey followed by a qualitative phase including focus groups and in depth interviews [23–26]. The research project will take place over 18 months and will occur in the following phases:

*Quantitative Phase 1*: *Understanding the primary health care model of care landscape (months 1 to 5)*: To document and map the range of primary health care services and models of care used in both countries, a cross sectional survey will be conducted with all humanitarian organizations in the health clusters (clusters are groups of humanitarian organizations, both United Nations and non-United Nations, in each of the main sectors of humanitarian action) in the study areas who are willing to respond (Fig 1). The cross sectional survey will target project managers and senior staff in humanitarian organizations. A purposive sampling method will be used to recruit all organisations willing to participate. A list of humanitarian organisations will be obtained from the humanitarian sector or clusters. From this list, an email invite with a link to the online survey will be sent to all the organisations inviting them to participate in the study. Face-to-face meetings will also be used to recruit and invite participants to take the online survey. One questionnaire will be administered per organization. Examples of survey variables will include organizational characteristics, models of care used, services offered, location of services, beneficiary populations (socio-demographics, ethnicity, gender, types of displacement).

**Fig 1 pone.0284957.g001:**
[figure not shown]
Flow chart of the research.

*Qualitative Phase 2a*: *Determining model of care selection factors (months 5 to 10)*: To explore the factors influencing the selection of primary health care models of care by humanitarian organizations in Cameroon and Nigeria (Table 2, mapping review results demonstrating existing models of care in both settings), a qualitative study using focus group discussions and in-depth interviews will be conducted (Fig 1). Study participants will include staff from humanitarian organization, ministry of health staff and internally displaced persons. Study participants from humanitarian organisations will be purposefully targeted and recruited using a screening tool with specific inclusion and exclusion criteria to identify the type of participants to be recruited for the in-depth interviews. A range of age, seniority, gender, roles, geography and types of primary health care models experienced will be enrolled through purposeful maximum variation sampling. Focus group discussions will be undertaken with internally displaced persons, identified through community facilitators used by humanitarian organizations. For the Focus group discussions, a local level mapping process will be conducted with key informants to determine the details of internally displaced persons residing within the district or local government area. A screening tool will be used to screen and identify internally displaced persons of different age, gender, ethnicity and/or socio-economic status. The in-depth interviews will be mapped according to the number and details of available groups of in-depth interviews at the districts/local government area, origin and occupation. Targeted sampling will be used to recruit participants for the in-depth interviews and focus group discussions. An minimum total of 30 in-depth interviews and 10 focus group discussions will be conducted in both countries. Interviews will be conducted until saturation is achieved. Themes to be explored during interviews with humanitarian organisations and ministry of health staff include location of interventions, security and access, community engagement, health facilities’ functionality, acceptability of models, barriers to accessing care, displacement patterns, ministry of health priorities, and funder priorities, barriers to health care.

**Table 2 pone.0284957.t002:** Mapping review results demonstrating models of primary health care and services offered in Cameroon and Nigeria.

Models of PHC care	Services offered	Cameroon (N)	Nigeria (N)
Community based interventions	Community based COVID-19 response, community management of HIV&TB, Essential health services, Early warning and alert system (EWARS), Health promotion, reproductive health	7	17
Mobile clinics	Essential health services, EWARS, immunization, mental health, reproductive health	17	35
Outreach	Immunization, mental health, reproductive health	0	17
Health Facility Based	Emergency care, Essential health services, immunization, reproductive health	1	44
Mobile Clinics & Health facility based	Essential Health services, reproductive health,	1	33
Government services	Immunization	9	0

For internally displaced persons, themes to be explored include; different strategies (models of care) available, models of care accessibility, community participation in model of care design and selection.

*Qualitative phase 2b*: *Determining the quality of care gaps (months 10–15)*: To determine the coverage and gaps in services across the different primary health care models, we will undertake further in-depth interviews with front line humanitarian program staff, ministry of health district staff and internally displaced persons [5, 27]. For the in-depth interviews, purposeful sampling will also be used to enroll participants of different ages, sex, ethnicity and displacement status. A minimum of 10 in-depth interviews will be conducted; interviews will be conducted until saturation is achieved. Themes to be explored will include gaps in service provision and quality of care (focusing on the quality of care domains: patient centered, safe, equitable, effective, integrated, timely and efficient). Same themes will be explored for both the different groups of study participants. However, the questions for IDPs will be simplified.

*Interpretation Phase*: *Triangulation of data from quantitative and qualitative phase*, *and developing the model of care framework (months 15–18)*: This final phase of the research will involve integrating results from both the quantitative phase and qualitative phase to inform the development of the framework to guide the selection of primary health care models and a “quality toolkit” for monitoring a pragmatic set of quality interventions for the different models of care in conflict settings (Fig 1). The framework will be developed during consultative workshops with key stakeholders from humanitarian organizations, government, and communities. This workshop will be organized to first share results of the studies conducted (for contextual validation) and to collectively design a quality toolkit for monitoring service delivery with different models of care. A total of two workshops with at least 30 participants each will be conducted.

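### The coverage part of Objective 3 is assigned only to purposive interviews, which cannot measure coverage at any sample size; the survey that could describe service presence is not assigned to it

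*Protocol article*

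**What the plan says.** The last of the three specific objectives in the Background is "3) to determine the coverage and gaps in services". The Conclusion repeats it and, like the Study design section, adds that this is to be done across the different models.

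The method is given under Study design, Qualitative phase 2b: "To determine the coverage and gaps in services across the different primary health care models, we will undertake further in-depth interviews". On sampling: "For the in-depth interviews, purposeful sampling will also be used to enroll participants of different ages, sex, ethnicity and displacement status". On size: "A minimum of 10 in-depth interviews will be conducted; interviews will be conducted until saturation is achieved". The phase is headed "Determining the quality of care gaps (months 10–15", and its content is described as "Themes to be explored will include gaps in service provision and quality of care", organised around seven quality domains.

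The Methods paragraph of the Abstract assigns coverage and gaps to qualitative work more broadly: "Using in-depth interviews and focus group discussions with staff from humanitarian organizations and internally displaced persons". It does not name the survey for this purpose.

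The Phase 1 survey has the stated purpose of documenting and mapping services and models, which is Objective 1. Its example variables include "models of care used, services offered, location of services, beneficiary populations".

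**The concern.** In health services work, coverage ordinarily means a share: areas or people reached by a service, over all those that could be. It needs a numerator and a denominator. Interviewees chosen for variety of age, sex, ethnicity and displacement status supply neither. They can say what they see as missing and why, but not what fraction of an area is served or whether one model covers more than another.

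The results go on to inform a framework for selecting models of care and a quality toolkit. If the coverage aim stays as worded and only interviews serve it, informants' impressions could be read there as measured coverage by model. Meanwhile, survey data that could support a limited descriptive answer would be used for mapping alone.

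**Working it through.** The document gives no power or precision calculation for this objective, and none is needed. The check is on sizes, then on which method is paired with which aim.

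**Sizes (Study design; Sample size)**

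- In-depth interviews: at least 30 in Phase 2a and at least 10 in Phase 2b, so 30 + 10 = 40. The country split agrees: 18 + 22 = 40. The Phase 2b minimum of 10 therefore spans both countries.
- Survey: 20 + 20 in Cameroon and 40 + 10 + 10 in Nigeria, so 40 + 60 = 100 organisations, as stated.

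**Aim against method**

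1. *Verb.* Objective 2 is to explore; Objective 3 is to determine, across models. The second is worded as measurement and comparison.
2. *Method.* Study design gives Phase 2b interviews only. The Abstract gives interviews and focus groups. No section names the survey for Objective 3.
3. *Content.* The Phase 2b heading and themes cover gaps and quality. Coverage is in the stated purpose of the phase but in neither of these.
4. *Analysis.* Interview data are coded thematically (Data analysis, Qualitative data). That yields themes, not shares.
5. *Integration.* The Interpretation Phase brings survey and interviews together, but for the framework and toolkit. It does not say that the survey answers the coverage question.

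**Does sample size matter?** Coverage = (units with the service) / (all units in the study region). Purposive sampling defines no set of all units, so the ratio does not exist for 10 interviews, for 40, or for more. A confidence interval would mislead here. If 10 interviews were treated as a simple random sample with 5 positive, the exact 95% interval would be 18.7% to 81.3%. That assumes random sampling, which the plan does not use, and wrongly suggests that more interviews would solve the problem.

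**What the survey could support.** For a given service and model, let D be all districts or LGAs in the study regions and d those where at least one responding organisation reports the service. Then d/D is the share with reported presence. Organisations that do not respond can add districts to d but not remove any, so with D fixed and reports taken as accurate, d/D is an undercount. This fails if D is restricted: the Study setting section selects Cameroon communities with the most humanitarian operations, and using those as the denominator could push the share upward.

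**The case against.** The strongest reply has four parts.

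- *Coverage is never defined as a proportion.* True, and the article promises no rate. The working content of Phase 2b is plainly qualitative, so the phrase may simply be loose. If so, rewording is the remedy. The text as it stands still says determine, and across models.
- *A full protocol may define a coverage measure.* It may, and a missing definition is not held against the article. What the article does state is which method serves the aim, and no later definition can derive a share from interview transcripts.
- *The qualitative base is wider than 10 interviews.* This stands. Ten is a minimum, with saturation as the stopping rule. It follows at least 30 interviews and 10 focus groups in Phase 2a, whose themes overlap (access, facility function, barriers, models available). None of these has a denominator either.
- *The survey is integrated before the framework is built.* This also stands, so the framework does not rest on Phase 2b alone. The gap is that no section assigns the survey to Objective 3.

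A reader might go further and infer that 10 interviews over the five models of Table 1 and two countries leave one per combination (10 / (5 × 2) = 1), so that the phase is too small. The document does not support that. Saturation sampling does not fill cells, and one interviewee may speak about several models. Some combinations may hardly exist: Table 2 shows no outreach in Cameroon and has no home-visit row.

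**Conclusion.** The point holds for the coverage component of Objective 3 only. That component is paired with a method that cannot answer it, and the wording recurs in four places: the Abstract, the specific objectives, Phase 2b and the Conclusion. Its size is half of one of three objectives. No number of interviews changes this, because the defect is one of kind rather than precision.

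A reader might infer that Objective 3 as a whole cannot be answered. The document does not support that: purposive interviews continued to saturation are a reasonable way to study gaps in services and quality.

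The conclusion assumes that coverage carries its usual meaning of a share reached. If the authors mean something looser, the defect reduces to wording, and the same text still needs changing. It should be fixed, but it does not threaten the rest of the study.

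**What to change.** 1. **Assign Phase 1 to the coverage part.** From the survey variables on models, services and locations, report for each service and model the number of districts or LGAs with at least one responding provider, over all districts or LGAs in the North West and South West regions of Cameroon and the North East Nigeria study states. Do not limit the denominator to communities selected for high activity.
2. **Record location at district or LGA level.** The article lists location as a survey variable without giving its resolution. The preliminary mapping review recorded it by district or division, so this looks feasible.
3. **Label the result.** Call it reported service presence among responding organisations, an undercount under non-response. It is not population coverage: it does not count people reached, and no population in need is listed among the survey variables.
4. **Reword the qualitative aim.** In Phase 2b, the Abstract, Objective 3 and the Conclusion, say that the interviews explore gaps in services and in quality as informants perceive them.

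The cost is one extra descriptive table, a check on how the questionnaire records location, and a more modest stated objective. No extra interviews are needed. If the authors do not want a coverage table, dropping coverage from the objective and making change 4 would also remove the mismatch, but the question would then go unanswered.
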